### Samples

Blood samples (up to 50 mL, venepuncture), urine (micturition) and saliva (spit) will be taken prior to surgery.During surgery, tissue samples will be taken as specified below.In women opting in, an additional endometrial biopsy will be taken during a follow-up visit at least 3 months after surgery. This can be done in an outpatient setting, and the taking of an endometrial biopsy in this setting using an endometrial sampling device (eg, pipelle or curette) is an established technique. A blood and urine sample will be taken again also.

### Participants

In each of the disease arms (endometriosis or fibroids), we plan to recruit up to 1200 women of reproductive age (18 years until menopause) who are planned to undergo surgery. Eight hundred of these will have the condition of interest, and 400 will be having surgery for other reasons and act as controls. In addition, we will include fibroid and uterine tissue samples collected as excess tissue (Oxford Radcliffe Biobank, REC Ref 09/H0606/5+5), currently approximately 70 samples.

### Inclusion criteria

The participant is willing and able to give informed consent for participation in the study.The participant is female and aged 18 years or above (before menopause).Women undergoing planned surgery (including hysterectomy) for endometriosis-associated and/or fibroid-associated symptoms such as abdominal pain, abnormal uterine bleeding or for unrelated gynaecological conditions (eg, fertility investigation or for laparoscopic tubal sterilisation).

### Exclusion criteria

The participant may not enter the study if ANY of the following apply:

Women who are pregnant.Women who are unable to read, or to understand written or spoken English.History of cancer/diagnosis of current cancer.

### Participant enrolment

#### Recruitment

After general information through a generic letter with information about ongoing research, which every patient will receive prior to her outpatient appointment, eligible women will be identified initially by the research nurses or clinical team during clinic visits. The study research nurses will then contact those women interested in participating in the study.

#### Screening and eligibility assessment

Women attending clinic appointments for endometriosis-associated and fibroid-associated symptoms such as pain, abnormal uterine bleeding and infertility will be asked to participate by clinical staff or by the authorised study research nurses. Women undergoing surgery for these conditions, and women undergoing surgery as part of their normal clinical management (eg, laparoscopic tubal ligation or hysterectomy; they would be the control patients) are eligible to participate in the study.

#### Informed consent

Prior to giving consent, and usually during their pre-operative assessment visit, women will be given the relevant patient information sheet and consent form to read. Written consent will be received by a trained member of the research team.

Written versions, with verbal explanations, of the patient information sheet and the consent forms will be presented to the participants detailing the exact nature of the study; what it will involve for the participant; the implications and constraints of the protocol; the known side effects and any risks involved in taking part. It will be clearly stated that the participant is free to withdraw from the study at any time for any reason without prejudice to future care, without affecting their legal rights, and with no obligation to give the reason for withdrawal.

The participant will be allowed as much time as wished to consider the information, and the opportunity to question the Investigator, their general practitioner (GP) or other independent parties to decide whether they will participate in the study.

Written informed consent will then be obtained by means of the participant’s dated signature and the dated signature of the person who presented and obtained the informed consent. The person who obtained the consent will be suitably qualified and experienced, and will have been authorised to do so by the Chief Investigator (CI). A copy of the signed informed consent and the patient information sheet will be given to the participant. The original signed form will be retained at the study site. The consent form for this study allows for the participant declining consent for any procedure that she is not comfortable with, while remaining eligible as a participant of the study, for example, if a participant did not want a uterine biopsy used in the study, she would not initial the corresponding box on the consent form, and insert ‘no’ instead.

### Study settings

#### Baseline assessments

Consented participants will be asked by the research team to complete a baseline questionnaire before their surgery. This may be sent to them for example, via mail or email before surgery or given to them in paper form in the clinic. Alternatively, participants have the option to complete an online version of the questionnaire or they may fill in the questionnaire on their handheld device. Each participant will receive a unique login for the online questionnaires.

The questionnaire data will be withheld from the research team until written informed consent is obtained and will be destroyed if this is not granted.

All participants will be sent further questionnaires at different time points (approximately 6–8 weeks, 6 months, 12 months and then yearly for 5 years after surgery). Participants may be reminded (twice, maximally) to return completed questionnaires via mail, email, phone or text or similar.

On the day of surgery, they will be asked to provide a mid-stream urine and a saliva sample. In addition, blood will be collected by peripheral venepuncture. The procedures will be explained to the women again and they will be given the opportunity to ask questions. Assessment of the presence and extent of disease will be performed by the operating surgeon.

Samples that may be taken at time of surgical procedures are as follows:

*Laparoscopy for suspected endometriosis*: endometrial biopsy, peritoneal fluid aspiration, fat tissue biopsy, endometriotic tissue if present, peritoneal biopsy.*Laparoscopy for uterine fibroids*: endometrial biopsy, peritoneal fluid aspiration, fat tissue biopsy, endometriotic tissue (if present), peritoneal biopsy, fibroid tissue, myometrial biopsy.*Laparotomy for uterine fibroids*: endometrial biopsy, peritoneal fluid aspiration, fat tissue biopsy, endometriotic tissue if present, peritoneal biopsy, fibroid tissue, myometrial biopsy.*Transcervical resection of uterine fibroids*: endometrial biopsy, fibroid tissue, myometrial biopsy.*Laparoscopy for tubal sterilisation (controls)*: endometrial biopsy, peritoneal fluid aspiration, fat tissue biopsy, peritoneal biopsy, myometrial biopsy.*Hysterectomy*: whole uterus as excess tissue from women with fibroids as well as from controls without fibroids, who undergo surgery for other indications (such as heavy menstrual bleeding, or pain), peritoneal fluid aspiration, fat tissue biopsy and peritoneal biopsy.

Women undergoing hysterectomy for benign causes such as abnormal uterine bleeding or pain will be asked to donate part of their uterus for research. Hysterectomy specimens are excess tissue and would be discarded otherwise.

During surgery, the surgeon will record digital photographs of the inside of the abdomen and/or uterine cavity as part of routine clinical care, which will also be stored on a secure server identified by the participant’s study ID. Intraoperative findings will be recorded by the surgeon and anonymised data collected.

### Subsequent visits

Unless participants underwent a hysterectomy, all included women will be asked to contact the study team when the next menstrual period after the procedure started. Together with the last menstrual period date given at the time of the procedure, this date will be used to calculate the length of the cycle. This is important in order to account for the changes that occur in the uterus during the menstrual cycle, and to enable us to distinguish between the effects of the cycle and the disease.

One subsequent visit will be made by participants treated for fibroids who consent to this. They will have another endometrial sample taken at least 3 months after the surgical intervention in an outpatient setting. The taking of an endometrial biopsy in this setting using an endometrial sampling device (eg, pipelle or curette) is an established technique, takes approximately 30 min and there is only a minimal risk of bleeding. In addition, blood and urine samples will be taken also. Pregnant women will not be eligible for the subsequent visits.

All women will be contacted by a member of the medical or study team and asked to fill in further questionnaires at different follow-up time points (approximately 6–8 weeks, 6 months, 12 months and yearly thereafter for a total of 5 years). Reminders will be sent twice, maximally. Women will also be asked if they can be contacted in the future for any further studies approved by an ethics committee.

#### Sample handling

Samples will be obtained according to WERF/EPHect guidelines^14–17^ by the interventions listed below. Only the study team will have access. Biological samples will be stored at −20°C or at −80°C for use in current and future studies until exhausted. Disease and control samples will be stored under the same conditions. For the purposes of this study, samples may be analysed at Oxford, or they may be transferred to a third party/study collaborator, including industrial partners, for analysis at their facility. If participants agree, samples will be moved to a Research Tissue Bank at the end of the study or stored and used in future ethically approved studies. They would be made available in anonymised form.

To investigate the relationship between uterine fibroids and symptoms such as abnormal uterine bleeding and pain, we aim to collect endometrial and myometrial samples alongside the fibroids themselves, to be able to detect the effects of fibroids on their surroundings.

We also intend to use the endometrium and endometriotic samples, one of the blood samples and fat samples to look for genetic factors and molecular pathways that can lead to endometriosis or uterine fibroids. The samples for this analysis will also be anonymised so that we do not know specifically which patient they came from. However, all samples are identifiable with printed label and location detail, participant ID, sample type and colour-coded cap.

#### Blood

Fifty millilitres. These are divided into (at least) EDTA-treated (2×9 mL) and heparin-treated samples (2×6 mL, both anticoagulation), serum (2×serum-separating tubes (SST), 5 mL) and two plain blood samples of 5 mL. The different vials are colour-coded and frozen at −80°C.

#### Urine

Twenty millilitres. Half of the sample will be used to test for glucose by specific gravity assay, the other half will be stored for the study. One aliquot of 5 mL is frozen directly at −80°C; 1 mL is centrifuged at 300 g and 5 aliquots of 200 µL of cell-free supernatant are frozen at −80°C.

#### Saliva

A spit sample of approximately 1 mL is taken on ice. One aliquot of 200 µL is frozen at −80°C, the rest is centrifuged at 300 g and 2×200 µL of cell-free supernatant are frozen at −80°C. One aliquot of 50 µL of cell-free supernatant is combined with 200 µL of RNA-preserving buffer (RNA later, Qiagen, Germany) and then frozen at −80°C.

#### Peritoneal fluid

During surgery, the peritoneal fluid will be collected by the surgeon using a syringe or through mechanical suction on ice. Depending on the volume (up to 15 mL), an aliquot will be centrifuged at 300 g, and the pellet (cells) stored at −80°C for further analysis. The cell-free supernatant will also be stored at −80°C.

#### Endometrium (eg, pipelle or curette), endometrial lesions (peritoneum), abdominal fat, myometrium, fibroid tissue

All tissue will be collected on ice and divided for storage at −80°C and—after fixing in paraformaldehyde and ethanol—at room temperature. Parts of fresh tissues will be used for culturing experiments, in order to test compounds, drugs or similar agents on primary cells.

#### Hysterectomy

In agreement with the local pathologist, whole uteri will be taken on ice and used for perfusion experiments within 24 hours before being transferred to pathology. Tissue samples of myometrium, endometrium, fibroid and fibroid-associated vasculature (if present) will be taken and stored at −80°C and—after fixing in paraformaldehyde and ethanol—at room temperature as the other tissue samples above.

### Assays

#### RNA analysis

RNA from each sample will be isolated by standard methods. Gene expression studies will be carried out between cases and controls (eg, endometriosis vs non-endometriosis patients, or fibroid-bearing women vs women without fibroids) using quantitative real-time PCR assays, whole RNA sequencing methods and RNA microarrays.

#### Protein analysis

Proteins will be extracted from tissue samples using standard methods. The expression and amount of proteins will be analysed by immunoblotting for specific proteins of interest, and by proteomics methods using the matrix-assisted laser desorption/ionisation/surface-enhanced laser desorption/ionisation platform. Tissue sections will be used in standard immunohistochemistry to detect the expression of markers of interest in situ.

#### Cells

Fresh tissue will be dissociated into single cell suspensions. From these, the diverse cell types (eg, endothelial cells) will be grown in incubators in vitro in order to study differences in cell behaviour between cases and controls, and to test compounds and drugs. Cells will be analysed by microscopy, flow cytometry and immunocytochemistry methods.

Similarly, cells isolated from peritoneal fluid or blood will be analysed using these methods.

#### Secretome analysis (perfusion)

Whole uteri with and without fibroids will be perfused with a suitable buffer for up to 8 hours. The perfusate will be analysed by proteomics methods (see above) to detect factors secreted by the fibroids.

#### Microscopy

Tissue blocks (up to 5 mm³ in size) from perfused uteri will be stained with antibodies against markers of blood vessels and fibroids, and leakiness, and be recorded in a confocal microscope in order to render a three-dimensional image of the blood vessels in situ. The detailed study of these will allow us to determine whether there is a significant difference in the architecture of blood vessels in uteri with fibroids compared with those from uteri without fibroids.

### Discontinuation/Withdrawal of participants from study

Each participant has the right to withdraw from the study at any time. In addition, the Investigator may discontinue a participant from the study at any time if the Investigator considers it necessary for any reason including:

Pregnancy;Ineligibility (either arising during the study or retrospectively, having been missed at screening);Withdrawal of consent;Loss to follow-up;Loss of mental capacity.

*Withdrawal from the study*: at the point the participant withdraws from the study, we will ask for consent to retain samples and data collected up to that point. Withdrawn participants will not be replaced. The reason for withdrawal will be recorded in the case record file (CRF).

#### Definition of end of study

The end of study is 6 months after the locking of the study database, to allow for completion of data analysis.

### Patient and public involvement

FENOX was built on experience and feedback we received from patients and research nurses during a previous study (a study to identify possible biomarkers in women with Endometriosis at Oxford^18^). In addition, the research objectives were set in accordance with research priorities identified through the James Lind Alliance Priority Setting Partnership (PSP) for endometriosis, in which we participate.^19^ The James Lind Alliance brings patients, carers and clinicians together in PSPs to identify and prioritise the top 10 unanswered questions or evidence uncertainties that they agree are the most important.

## Interventions

### Non-clinical interventions

#### Questionnaires

Participants will complete specific questionnaires about their condition, general health, pain sensitivity, medication and menstrual history before their surgery. Additionally, those women with endometriosis will be asked to complete the Endometriosis Health Profile (EHP-30) Questionnaire,^20^ while women with fibroids complete a section on their quality of life.^21^ Currently, the clinical questionnaires are completed by participants on paper; in the future, the aim is that the questionnaires can be completed via a handheld device or via the internet directly onto a secure server. For this, women will receive a pretrial study number and login information. The follow-up questionnaires ask about symptoms and changes in menstrual history as relevant. The control groups would be given the same questionnaires as the women with the respective condition and asked to omit questions not applicable to them.

#### Medical records

We will obtain clinical data (menstrual cycle phase, medication, pain and menstrual bleeding status, photos from surgery) from the patients’ medical records.

### Clinical interventions

#### Venepuncture

Taken by an appropriately trained member of the clinical or research staff.

#### Collection of other bodily fluid sample

Urine and saliva samples donated by the patient and sample prepared and analysed by a member of the investigative team.

#### Tissue collection

Tissue/fluid (eg, fibroids if present) will be collected as part of routine surgical management apart from:

#### Laparoscopy

Peritoneal fluid will be aspirated, biopsies from endometrium (eg, pipelle or curette), abdominal fat tissue, myometrium and peritoneum (excision) will be taken during surgery.

#### Additional risk

Minor bleeding, uterine perforation (<1%), additional length of surgery by 5 min.

### Myomectomy/Hysterectomy

Endometrial, myometrial and/or fibroid tissue biopsies will be taken during surgery. Hysterectomy samples will be used in structural analysis assays ex vivo in close discussion with the clinical pathologists.

*Additional risk*: minor bleeding, uterine perforation (<1%), additional length of surgery by 5 min.

#### Transcervical resection of fibroids

Endometrial and myometrial biopsies will be taken during surgery.

*Additional risk*: minor bleeding, uterine perforation (<1%), additional length of surgery by 5 min.

#### Additionally

In women opting in, an additional endometrial biopsy will be taken during a follow-up visit in an outpatient setting. The biopsy of the endometrium is a simple, routine procedure and takes about 30 min.

*Additional risk*: minor bleeding, uterine perforation (<1%), short period of discomfort.

Women will be asked to consent to the use of samples and clinical data collected as part of this research and in future research. Women, if they consent, will potentially be contacted for future studies approved by an ethics committee.

### Adverse events

For this study, it is conceivable that additional procedures may result in bleeding. However, if this resulted in a scenario mentioned below, it would constitute a serious adverse event (SAE) and needed to be reported to the sponsor.

An SAE is any untoward medical occurrence that:

results in death;is life-threatening;requires inpatient hospitalisation or prolongation of existing hospitalisation;results in persistent or significant disability/incapacity;consists of a congenital anomaly or birth defect.

Other ‘important medical events’ may also be considered serious if they jeopardise the participant or require an intervention to prevent one of the above consequences.

*Note*: The term ‘life-threatening’ in the definition of ‘serious’ refers to an event in which the participant was at risk of death at the time of the event; it does not refer to an event which hypothetically might have caused death if it were more severe.

An SAE occurring to a participant should be reported to the REC that gave a favourable opinion of the study where in the opinion of the CI the event was ‘related’ (resulted from administration of any of the research procedures) and ‘unexpected’ in relation to those procedures. Reports of related and unexpected SAEs should be submitted within 15 working days of the CI becoming aware of the event, using the Health Research Authority (HRA) report of SAE form (see HRA website, https://www.hra.nhs.uk).

### Data analysis plan

As this is a prospective sample and data collection study, there is no randomisation of patients as all women will undergo surgery as part of their routine clinical management. As previously,^18^ we will use SPSS, GraphPad Prism, STATA and R for analysis, and employ t-tests, analysis of variance (ANOVA), correlation coefficient analysis and similar methods. We plan to use multivariate logistic regression models in comparisons of endometriosis cases with controls, and fibroid cases with controls, adjusting for confounders relevant to the hypothesis being tested. A priori confounders are likely to be age, ethnicity and menstrual cycle phase. Patients with both endometriosis and fibroids will enter into the analysis according to the research question asked; we will conduct sensitivity analyses on this comorbid group to examine to what extent they influence the results. Due to the exploratory nature of this study, various additional statistical techniques may also be used to fully explore the relationships in the data, but all methods will be fully documented.

### Power calculations

Power calculations were done in R (V.3.6.1) using the *pwr* package. For our primary outcome, we plan to correlate questionnaire and laboratory data. To detect correlations with a moderate effect size of r=0.3 at a power of 80% and 0.05 significance level, we will need 85 samples per group (*pwr.r.test*). For the detection of effect sizes of at least 0.2 between groups (eg, endometriosis cases vs controls, with three cycle phases and five disease stages (0, stages 1–4)) using ANOVA at 0.05 significance and 80% power, at least 32 samples per groups will be used, with a total of 480 samples for all 15 groups (*pwr.anova.test*). Multiple comparisons will be corrected for by Bonferroni’s method.

### The number of participants

It is now recognised that both endometriosis and uterine fibroids are very heterogeneous conditions. Our previous studies^22 23^ and systematic reviews^24 25^ have clearly identified a lack of sufficiently powered studies. Multiple large-scale research collaborations are currently in place investigating different aspects of endometriosis,^26^ and we plan similar efforts for uterine fibroids. Therefore, large patient numbers are needed.

The Endometriosis CaRe Centre at Oxford is the UK’s largest endometriosis centre. Similarly, as a tertiary referral centre, we see many women with fibroid-associated symptoms. As a result, we have the unique opportunity to collect large amounts of data and samples, which is essential to produce clinically meaningful outputs. Given our current patient recruitment rate (endometriosis: 100/year, uterine fibroids, 200/year), we estimate an enrolment of approximately 2×1200 women over the course of the study (800 endometriosis patients+400 non-endometriotic controls, 800 fibroid patients+400 non-fibroid controls). Fibroids already collected as excess tissue under the Oxford Radcliffe Biobank (REC Ref 09/H0606/5+5) will also be included in this study, currently approximately 70 samples.

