**Methods and analysis:**

Biological samples such as blood, saliva, urine, fat, peritoneal fluid and—if found—endometrial tissue or fibroids as well as detailed clinical and intraoperative data will be collected from women undergoing surgery and participating in the study after informed consent. We plan to recruit up to 1200 participants per disease arm (ie, endometriosis and uterine fibroids) over 5 years. Participants will fill in detailed and validated questionnaires on their medical history and quality of life, with follow-ups for 5 years. Enrolment started on 2 April 2018, and FENOX will close on 31 March 2028. We will analyse the biological samples using state-of-the-art molecular biology methods and correlate the findings with the medical records and questionnaire data.

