### Outcomes

#### Primary outcome

We will used questionnaire data, medical records and sample analysis to investigate the genetic and molecular basis of the pathogenesis and symptoms of endometriosis and uterine fibroids. At the end of the recruiting period, that is, from December 2022 onwards, the collected data and samples will be analysed and compared between endometriosis/fibroid cases and non-affected controls.

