**Figure 2 F2:**
[figure not shown]
Flow chart of participant data and tissue sampling. Consented participants of the different arms of the study donate pre-operative samples and fill in a baseline questionnaire. They can donate a range of tissue samples according to their condition and treatment mode (eg, fibroids or endometriotic tissue, peritoneal fluid), and are asked to repeatedly fill in follow-up questionnaires on their condition and quality of life, so that the clinical findings can be correlated with the outcome years later.

Blood, saliva and urine will be taken prior to surgery. Tissue and peritoneal fluid (where applicable) will be taken at the time of the scheduled surgery.

In order to determine the effect of the surgical removal of the fibroids on the local tissue, it is necessary to take an additional endometrial biopsy after the planned surgical intervention. This sample will be timed to synch with the same time point in the menstrual cycle that the original sample was taken, and thus will give us a unique insight into the biology of the conditions. During this visit, blood and urine samples will be taken again also. Women can opt in or out of the additional clinic visit where these samples would be taken.

Women will be asked to complete questionnaires on paper, online or into their electronic handheld devices (health, pain, medication and, initially, ethnicity) at different time points. There will be a lengthy questionnaire at baseline before surgery (taking an estimated 45 min to complete), and shorter versions (taking up to 30 min to complete) postoperatively at 6–8 weeks, 6 months, 12 months and thereafter yearly for a total of 5 years after surgical intervention.

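### The endometriosis enrolment estimate (800 cases plus 400 controls) does not follow from 100 recruits a year over a recruiting period of about 4.7 to 5 years

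*Protocol article*

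**What the plan says.** The section on the number of participants presents the size as a consequence of observed accrual: "Given our current patient recruitment rate (endometriosis: 100/year, uterine fibroids, 200/year), we estimate an enrolment of approximately". The total that it then gives, for both arms and with the split into cases and controls, is "2×1200 women over the course of the study (800 endometriosis patients+400 non-endometriotic controls, 800 fibroid patients+400 non-fibroid controls". The Participants section repeats the split within each arm: "Eight hundred of these will have the condition of interest, and 400 will be having surgery for other reasons and act as controls".

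The recruiting period is given in two places. The abstract (Methods and analysis) says "We plan to recruit up to 1200 participants per disease arm (ie, endometriosis and uterine fibroids) over 5 years", and then "Enrolment started on 2 April 2018, and FENOX will close on 31 March 2028". The primary outcome section places the start of the analysis "At the end of the recruiting period, that is, from December 2022 onwards". The Study design section, after Figure 2, sets questionnaires at "12 months and thereafter yearly for a total of 5 years after surgical intervention".

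The power section uses neither 800 nor 1200. It asks for 85 samples per group for correlations, and for 32 samples in each of 15 groups (three cycle phases by five disease stages, stage 0 included), 480 in all, for the ANOVA.

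**The concern.** The article prints a rate, a duration and a total, and says that the total rests on the rate. For endometriosis the three do not agree. This is not an omission that a fuller protocol would fill, because all the figures are on the page.

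What is at stake is how many endometriosis cases a reader should expect. The same section justifies large numbers by a lack of adequately powered earlier studies. The endometriosis arm also carries the biomarker objective and the stage-by-phase example in the power section. If the arm ends well below its stated size, any analysis planned around 800 cases starts from a number that the stated accrual does not supply. Whether the power section's own, smaller requirements are at risk depends on what the rate counts.

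**Working it through.** **Inputs**
- Rates: endometriosis 100 a year, fibroids 200 a year (number of participants).
- Target per arm: 800 cases + 400 controls = 1200 (number of participants; Participants).
- Start: 2 April 2018 (abstract).
- Recruiting time: 5 years (abstract), or to December 2022 (primary outcome). To 1 December 2022 is 4.67 years; to 31 December 2022 is 4.75 years.

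**Trying to reproduce the plan's figure.** Recruits = rate × recruiting time.

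| Recruiting time | Endometriosis (100/year) | Fibroids (200/year) |
|---|---|---|
| 4.67 years | 467 | 933 |
| 4.75 years | 475 | 949 |
| 5 years | 500 | 1000 |
| Stated | 800 cases, 1200 in all | 800 cases, 1200 in all |

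No row gives 1200 in either arm, and no row gives 800 for endometriosis.

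**Time and rate needed.** Endometriosis: 800/100 = 8 years for the cases, 1200/100 = 12 years for the whole arm. In 5 years these need 800/5 = 160 and 1200/5 = 240 a year. Fibroids: 800/200 = 4 years for the cases, 1200/200 = 6 years for the whole arm.

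**Two readings of the rate.** The article does not say whether controls are counted.

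*Cases only.* Endometriosis cases are 467/800 = 58% to 500/800 = 63% of target. Fibroid cases (933 to 1000) exceed 800.

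*Whole arm.* The endometriosis arm is 467/1200 = 39% to 500/1200 = 42% of target. At 2:1 this is 467 × 2/3 = 311 to 500 × 2/3 = 333 cases, with 156 to 167 controls. The fibroid arm is 933/1200 = 78% to 1000/1200 = 83% of target.

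**Against the power section.** The ANOVA needs 15 × 32 = 480 samples. Stages 1 to 4 by three phases make 12 case cells, 12 × 32 = 384 cases. Stage 0 makes 3 cells, 3 × 32 = 96 controls.

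| Reading | Cases (need 384) | Controls (need 96) | 85 per group |
|---|---|---|---|
| Cases only, 2:1 controls added | 467 to 500: met | 233 to 250: met | met |
| Whole arm, 2:1 | 311 to 333: not met | 156 to 167: met | met |

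Where the case total is met, this assumes that stages and phases fill evenly. On the whole-arm reading the average is 311/12 = 26 to 333/12 = 28 per case cell, against 32.

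**End date.** Five years from 2 April 2018 runs to about the start of April 2023. The primary outcome section says December 2022. The two differ by three to four months.

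**The case against.** *1200 is a ceiling.* The abstract and the Participants section do say up to 1200. The section on the number of participants does not. It gives an approximate estimate and names the current rate as its basis, so the ceiling wording does not repair it.

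*The estimate is for the whole study, not 5 years.* Ten years to the March 2028 close would give 100 × 10 = 1000 endometriosis recruits. That is above 800 if only cases are counted, and still below 1200 if the whole arm is. But it contradicts both statements of the recruiting period. Women operated on after about March 2023 also could not complete 5 years of follow-up by the close.

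*Other sources of cases.* Incidental diagnoses move women into the relevant case group (Study design), and the Discussion reports expansion beyond Oxford. Both are real possibilities, and neither has a rate. If fibroid recruits alone had to close the gap on the cases-only reading, (800 − 500)/1000 = 30% to (800 − 467)/933 = 36% of them would need endometriosis not already counted in the 100 a year. In the other direction, the Figure 1 legend moves women found without endometriosis to the controls. The roughly 70 biobank samples are fibroid and uterine tissue and do not help this arm.

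*The study is exploratory, and its power section does not depend on 1200.* This stands in part. It limits the consequence: on the cases-only reading every total in the power section is still met. It does not make the estimate correct.

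*A calendar conflict that a reader might infer.* One could equate the 31 March 2028 close with the end of study, defined thus: "The end of study is 6 months after the locking of the study database". That would imply a lock by about September 2027 and lost 5-year questionnaires. The article nowhere equates the two dates. Five years of recruiting plus 5 years of follow-up from 2 April 2018 ends almost exactly at the stated close, so lock may simply follow it. That inference is not supported.

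**Conclusion.** The point holds for the endometriosis arm. At the stated rate and recruiting period it gains about 467 to 500 women. That is about 60% of the 800 cases on the reading kindest to the plan, and about 40% of 1200 (roughly 311 to 333 cases) if the rate covers cases and controls. This assumes that the current rate continues and that recruiting lasts 4.67 to 5 years.

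Two wider conclusions are tempting but not supported. The first is that both arms fall short, or that the pooled total is 1500 against 2400. That needs the rates to include controls, which the article does not say; the fibroid case target is reachable if they do not. The second is that every planned analysis loses its basis. The 85-per-group requirement is met on either reading, and the 480-sample ANOVA is in doubt only on the whole-arm reading, or if cells fill unevenly.

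What remains is a stated sample size that its own stated basis does not deliver, and a recruitment end date given two ways. Both need correcting.

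**What to change.** In the section on the number of participants:
1. Restate the expected enrolment from the stated rates, about 470 to 500 endometriosis and 930 to 1000 fibroid recruits. Alternatively, give the rates and sites that would yield 2×1200.
2. Say whether 100 and 200 a year include controls.
3. Keep 1200 per arm only as a ceiling, here as in the abstract and the Participants section.
4. Set the restated case and control numbers against the power section: 85 per group, and 384 cases plus 96 controls for the ANOVA. State what is assumed about how the stage-by-phase cells fill.
5. Use one recruitment end date in the abstract and the primary outcome section (December 2022, or about April 2023).

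The cost is protocol wording. No extra participants or procedures are needed, though the stated endometriosis figure becomes less favourable unless added sites or rates are documented.
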